| RELEVANT METHODS | 
ARD patients and controls will be vaccinated with the vaccine against COVID-19 by HCFMUSP.
 
The vaccination protocol will consist of two doses of the COVID-19 vaccine for patients and controls, in addition to the collection of a blood sample on the day of the 1st vaccine dose (D0), on the day of the 2nd vaccine dose (28 days after first dose) and 40 days after the second dose of the vaccine. An additional (third) dose will be given 6 months after the second dose (D210) and immunogenicity will be assessed 30 days later (D240). Blood collection will also be performed at D210 prior to vaccination (3rd dose) to assess humoral response decay.
 
The serum obtained during collection will be stored in a -70°C freezer for testing for immunogenicity.
 
Immunogenicity will be assessed using the seroconversion rates of total IgG antibodies against S1 and S2 antigens and neutralizing antibodies to SARS-CoV-2 on the day of the 2nd dose and 40 days after the 2nd dose, using the 2-dose vaccine schedule is 28 days apart. Additionally, immunogenicity will be assessed prior to the third dose vaccination, 6 months after the second dose, and 30 days after the third dose vaccine dose (6 months after the second dose).
 |

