|  | 
instructed to note in a standard diary the changes that occur in the period, such as:
 
Local reactions: pruritus, local pain, erythema, induration at the vaccine site,
 
Systemic reactions: tiredness, fatigue, headache, nausea, diarrhea, fever, chills, myalgia, arthralgia and diarrhea, signs of airway infections (cough, sputum, sore throat, ear pain or discharge, nasal congestion or expectoration, dyspnoea, sneezing), fever (axillary temperature > 37.8° C), itchy skin, rash, vertigo, abdominal pain, drowsiness, malaise, flushing, extremity pain / discomfort, back pain, edema, inappetence.
 
In addition, the need for medical care, hospitalizations, severity of infections, sick days, absenteeism at work and treatment received will be raised, regarding a clinical condition compatible with COVID-19.
 
The standardized diary of adverse events will be evaluated by the researchers 28 days after the first dose of vaccine and 40 days after the second dose. The diary includes guidance for telephone communication of any events that require hospital care. If tertiary care is required, the participant will be transferred to our University hospital (Hospital das Clínicas FMUSP). Serious adverse events will be defined as those that result in hospitalization or death. They will be reported to the National Ethics Committee (CONEP) within 24 hours.
 
Surveillance will be maintained for new cases of COVID-19 through weekly WhatsApp messages. For patients who present symptoms compatible with COVID-19 infection after vaccination, according to the recommended routine for monitoring immunosuppressed patients with a suspicious condition, a nasal swab will be collected to perform PCR for COVID, with sequencing
 |

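### Between diary reviews, serious adverse events not related to COVID-19 come to light mainly if the participant telephones, and the 24-hour reporting limit has no stated start

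*Protocol*

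**What the plan says.** All of the following is in the protocol, mostly in the SAFETY section.

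- **Definition.** "Serious adverse events will be defined as those that result in hospitalization or death".
- **Scheduled route.** The participant's diary is "evaluated by the researchers 28 days after the first dose of vaccine and 40 days after the second dose".
- **Unscheduled routes.** "The diary includes guidance for telephone communication of any events that require hospital care". In addition, a participant who needs tertiary care is moved to the study's own university hospital.
- **Questions on hospitalization.** Medical care, hospital stays, sick days and "treatment received will be raised, regarding a clinical condition compatible with COVID-19".
- **Weekly contact.** "Surveillance will be maintained for new cases of COVID-19 through weekly WhatsApp messages".
- **Reporting of serious events.** "They will be reported to the National Ethics Committee (CONEP) within 24 hours". The moment from which the 24 hours count is not given.
- **Later doses.** The RELEVANT METHODS section adds a third dose at D210 with an immunogenicity sample at D240. The OUTCOMES section adds a fourth dose for poor responders. Neither section, nor SAFETY, states a diary review after those doses.

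Safety in patients compared with controls is item 2 of the primary outcomes.

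**The concern.** A serious event is, by definition here, one in which the participant is in hospital or has died. Those are the circumstances in which a person is least able to telephone. No route through relatives or another contact person is stated. If no call comes and no transfer takes place, the next stated enquiry about adverse events is the diary review. The one regular contact that could fill the gap is described for COVID-19 cases only.

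Two things are at stake. The first is participant safety: the team may learn of an event late or not at all, and a 24-hour rule without a defined start cannot be audited. The second is the completeness of the serious-event counts behind a primary outcome.

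**Working it through.** The plan gives no figure to reproduce, so the check sets the routes side by side and then works out the waiting times.

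**1. Which events does each stated route reach?**

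| Route | Reaches | Leaves out |
|---|---|---|
| Telephone guidance in the diary | Events needing hospital care, if the participant can and does call | Death without a call; incapacity; events not called in |
| Transfer to the university hospital | Events needing tertiary care once the need is known | Admissions elsewhere that need no tertiary care; death outside hospital |
| Weekly WhatsApp message | By its stated purpose, new COVID-19 cases, including any admitted | Events unrelated to COVID-19 |
| Hospitalization questions | Illness compatible with COVID-19 | All other causes |
| Diary review | Any event recorded in the diary | Nothing by cause, but only at two time points |

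For an event unrelated to COVID-19, no row describes a routine active enquiry between the two diary reviews.

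**2. How long can an event go unnoticed if it is not telephoned or otherwise noticed?**

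Inputs: contact interval L = 28 days after dose 1 and 40 days after dose 2 (diary reviews, SAFETY); L = 7 days for a weekly message.

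Assumption, not in the protocol: the event is equally likely on any day of the interval. Then the longest wait is L, the mean wait is L/2, and the share found within 24 hours of occurrence is 1/L.

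| Contact | Longest wait | Mean wait | Found within 24 hours of the event |
|---|---|---|---|
| Diary, after dose 1 | 28 days | 28/2 = 14 days | 1/28 = 3.6% |
| Diary, after dose 2 | 40 days | 40/2 = 20 days | 1/40 = 2.5% |
| Weekly question, answered at once | 7 days | 7/2 = 3.5 days | 1/7 = 14% |

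The weekly question shortens the wait by a factor of 28/7 = 4 after dose 1 and 40/7 = 5.7 after dose 2.

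**3. What happens after the last stated review?**

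Dose 2 is on day 28, so the second review falls on day 28 + 40 = 68. The third dose is at D210. The stretch without a stated adverse-event review before that dose is 210 − 68 = 142 days. None is stated after it either.

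**4. What does the 24-hour limit mean?**

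If it runs from the event, the last column of the table shows that diary review alone would rarely meet it, and a weekly question would also usually miss it. If it runs from the team's awareness, it can be met however late awareness comes. The protocol does not say which applies.

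**The case against.** The strongest reply is that the protocol already has a working system: a definition, telephone guidance aimed at the hospitalization part of that definition, transfer to the study hospital, two scheduled reviews and a reporting limit. Message wording and follow-up calls are often set out in operating procedures or in the diary itself, which are not shown. Nothing in the protocol contradicts itself on this point.

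Much of that stands, and it rules out several stronger readings that a reader might infer:

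- **That telephone and diary are the sole routes.** They are not. Transfer for tertiary care is a further route, and the COVID-19 surveillance can bring COVID-19 admissions to light.
- **That events always surface 28 to 40 days late.** Those are the two maxima. The wait runs from 0 to 28 or from 0 to 40 days.
- **That the weekly message goes to everyone and asks about nothing else.** The protocol gives its purpose, not its text or recipients. The mention of up to 12 months follows the text on swabs and sequencing and may not describe the messages.
- **That the 24-hour rule cannot work.** Counted from awareness, it can.
- **That an event after dose 1 is known too late for anyone to act.** The first diary review falls on the day of dose 2, so the researchers see the diary at that visit.
- **That serious events are missed more often in controls, biasing the safety comparison.** The SAMPLE SIZE section places the rare-disease patients under follow-up at the hospital's rheumatology clinic and states nothing comparable for healthy controls. Unequal capture is therefore possible. But both groups receive the same diary instructions and no detection rates are given, so neither the bias nor its size is documented.

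The reply does not remove the central gap. The SAFETY section sets out how serious events are found, and it limits both the weekly contact and the hospitalization questions to COVID-19.

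**Conclusion.** The point holds in a limited form. As written, detection of serious events between diary reviews is mainly passive, and an admission or death unrelated to COVID-19 has no routine active enquiry. If it is not telephoned or otherwise noticed, it may stay unknown for up to 28 days after dose 1 or up to 40 days after dose 2. No review is stated after the third or fourth dose. The start of the 24-hour limit is undefined.

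The maxima follow directly from the schedule. The means and the 24-hour shares rest on the assumption of uniform timing. How many events would be affected cannot be estimated from the protocol, and no claim is made that the comparison of patients with controls is biased. The change is worth making because it is cheap and serves both participant safety and a primary outcome.

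**What to change.** Amend the SAFETY section in three places:

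1. Extend the existing weekly message, for patients and controls alike, with one question: any admission to hospital since the last message, for any reason.
2. Follow up persistent non-response with a call to the participant or a contact person. This is also how a death would come to light.
3. State that the 24 hours for reporting to the ethics committee run from the team's first awareness of the event, by whatever route.

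The period over which the messages run should be stated as well, because the change reaches the third and fourth doses only if the messages are still being sent then.

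This brings the longest wait down to about 7 days when messages are answered. It does not give 24 hours from occurrence. The cost is a protocol wording change, one line in a message already planned, and a small amount of staff time for follow-up calls.

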|                     | 
be 445 ARD patients and 89 healthy subjects, sex-matched and with similar ages. Expecting a higher SC rate of 98% for this vaccine, such sample size had a power greater than 99% to detect a 15% reduction in SC of ARD patients. Due to the peak of pandemics ongoing in Brazil during the vaccination period, we invited more patients and controls, expecting a high incidence of previously infected people and a high rate of infections.
 
A sample was calculated for patients with other rare rheumatological diseases, grouped into five diseases (systemic scleroderma, dermatomyositis/myositis, primary Sjogren's syndrome, systemic vasculitis and primary antiphospholipid antibody syndrome) being followed up in Rheumatology outpatient clinic (HCFMUSP). For the calculation, a seroconversion ratio of <math>p_1 = 50\%</math> is assumed for each disease and <math>p_2 = 74.25\%</math> as the average seroconversion of healthy controls. The sample size for each rare disease was 50, thus 250 being the number of patients with other diseases.
 
2. CONTROL GROUP: 271 healthy controls matched for age and sex will be included according to the need for controls for lupus (<math>n = 74</math>), rheumatoid arthritis (<math>n = 61</math>) and ankylosing spondylitis / psoriatic arthritis (<math>n = 136</math>) will be selected to receive the vaccine at HCFMUSP.
 |

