|  | 
for mutant strains in positive cases. for a period of up to 12 months after the 2nd dose of the vaccine. Positive samples will be sequenced by the protocol established at IMT-FMUSP (1) using the MinION platform (Oxford Nanopore Technologies, UK). The extracted RNA is converted into cDNA using the SuperScript IV First-Strand Synthesis System (Thermo Fisher Scientific, USA) and amplification of the complete genome using the Multiplex PCR protocol - version 3, described by Quick 2020 (2). The amplified samples are purified using 1x Ampure XP beads (Beckman Coulter, United Kingdom) and 70% alcohol solution twice. Amplicons are quantified with Qubit dsDNA High Sensitivity Assay Kit fluorophore and assayed in the Qubit 3.0 instrument (Life Technologies, USA (ThermoFisher) as recommended by the manufacturer. Amplicons are normalized to 240 ng and identified with barcodes. the following EXP-NBD104 (1-12) and EXP-NBD114 Native Barcoding Kits (Oxford Nanopore Technologies, UK) and Ligation Sequencing kit (ONT, SQK-LSK109) are used according to protocol (2). The final library is then loaded into the flowcell R9.4.1 and sequenced using the MinION platform (Oxford Nanopore Technologies - ONT) .The programs MinKNOW (version 19.10.1) and RAMPART are used to monitor the sequencing run in real time (https://artic.network/rampart)
 
After the end of the race, the fast5 files are subjected to base calls and separation of the barcodes (basecalled and demultiplexed) using the Guppy software, version 2.2.7 (Oxford Nanopore Technologies, UK). To obtain the consensus sequences, the fastq5 files are mapped against the reference genome of SARS-CoV-2 isolate Wuhan-Hu 1 (GenBank accession number MN908947) using the program minimap2 (version 2.28.0) and SamTools.
 |

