|-----------------------------|----------------------------------------------------------------------------------------------------------------------------------------------------------------------------------------------------------------------------------------------------------------------------------------------------------------------------------------------------------------------------------------------------------------------------------------------------------------------------------------------------------------------------------------------------------------|
|                             | Bioinformatics analyzes will follow the protocols described by the research group ARTIC ( https://artic.network/ncov-2019 ).                                                                                                                                                                                                                                                                                                                                                                                     |
| STATISTICAL ANALYSIS | The results will be presented as mean $\pm$ standard deviation (SD) or median for continuous variables and percentage for categorical variables. Data for continuous variables will be compared using Student's t-test or Mann-Whitney to assess differences in immunogenicity (serology) between patients with rheumatic diseases versus healthy controls. Differences between categorical variables (safety and effectiveness) will be assessed using the chi-square or Fisher's exact tests. Statistical significance will be established with $p < 0.05$ . |

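### COVID-19 cases are sought over follow-up of up to 12 months, but the only test named for effectiveness compares simple percentages and ignores time at risk

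*Protocol*

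**What the plan says.** Under STATISTICAL ANALYSIS the protocol reports a "percentage for categorical variables" and names one family of tests for them: "Differences between categorical variables (safety and effectiveness) will be assessed using the chi-square or Fisher's exact tests". It names no person-time, survival or censoring method.

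Under SAFETY, "Surveillance will be maintained for new cases of COVID-19 through weekly WhatsApp messages". People with compatible symptoms are swabbed, positives are sequenced, and this runs "for a period of up to 12 months after the 2nd dose of the vaccine". That wording sets a maximum, not a period common to everyone. The same section records medical care and hospital admissions for illness compatible with COVID-19.

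Other safety data have their own timing. The adverse event diary "will be evaluated by the researchers 28 days after the first dose of vaccine and 40 days after the second dose". On serious events, "Serious adverse events will be defined as those that result in hospitalization or death"; no 12-month window is attached to them.

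STUDY DESIGN describes an observational comparison with matched healthy controls. SAMPLE SIZE explains that extra people were invited "expecting a high incidence of previously infected people and a high rate of infections". No section gives an expected infection rate, a dropout rate, or a rule for people who stop answering.

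**The concern.** Immunogenicity has its own sentence in the analysis section, and infection is the only outcome in the protocol that fits the word effectiveness. The chi-square or Fisher rule therefore most naturally covers the COVID-19 cases found by surveillance.

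Those cases build up over time, and finding them depends on the participant staying in contact. A proportion test treats two months of observation like twelve. The groups are not randomised, and the protocol contains nothing to ensure equal retention over a year. If one group is observed for longer, it shows more cases at the same hazard. Depending on the direction, the analysis could report a patient excess that does not exist or weaken one that does.

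The point is not that a method is missing and might be found in the SAP. A method is stated, and it does not suit the follow-up that is stated.

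**Working it through.** **The protocol's own figures.** It gives no sample size or power for COVID-19 cases. Its 445 patients and 89 controls are for seroconversion (63% v 78%, 5:1, alpha 5%, power 80%). They reproduce with a two-sided pooled formula without continuity correction. The pooled rate is (0.78 + 5×0.63)/6 = 0.655, so controls = [1.960×√(1.2×0.655×0.345) + 0.842×√(0.78×0.22 + 0.63×0.37/5)]² / 0.15² = 88.8, rounded up to 89, and 5×89 = 445. These numbers serve below only as a scale.

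**Inputs.** From the protocol: chi-square at the 5% level; follow-up of at most 12 months; 445 patients; 271 planned controls. Assumed, because the protocol is silent: constant hazard, 12-month risk r = 15%, and a fraction L lost evenly over the year independently of infection.

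**Observed risk with everyone kept in the denominator.** h = −ln(1 − r) = −ln(0.85) = 0.1625. A person lost at a uniformly distributed time has mean observed risk m = 1 − r/h = 1 − 0.15/0.1625 = 0.0770. Observed risk = (1 − L)×r + L×m.

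- L = 10%: 0.9×0.15 + 0.1×0.0770 = 14.27%
- L = 30%: 0.7×0.15 + 0.3×0.0770 = 12.81%
- L = 50%: 0.5×0.15 + 0.5×0.0770 = 11.35%

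**Rejection rate of the uncorrected chi-square, equal true hazards, 445 v 271** (binomial counts simulated at these risks):

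- 20% v 20% lost (patients v controls): ratio 1.00, rejects 5%
- 10% v 30% lost: 14.27/12.81 = 1.11, rejects about 8%
- 10% v 50% lost: 14.27/11.35 = 1.26, rejects about 19%

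**The other usual denominator.** Drop people lost without a case but keep all observed cases: risk = observed risk / [(1 − L) + L×m]. For 10% v 50% lost this gives 0.1427/0.9077 = 15.7% for patients and 0.1135/0.5385 = 21.1% for controls. The false patient excess becomes a false deficit.

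**A real difference.** With a hazard ratio of 1.5 and control risk 15%, patient risk is 1 − 0.85^1.5 = 21.6%, so the risk ratio without loss is 21.6/15.0 = 1.44 and the test rejects about 60% of the time. With 30% of patients and 10% of controls lost, h = 0.2438 and m = 0.1126 for patients, so the observed risks are 0.7×0.2163 + 0.3×0.1126 = 18.5% and 14.3%. The ratio is 1.30 and the test rejects about 31%.

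**The alternative.** Expected person-years per participant equal the observed risk divided by h. At 10% and 50% lost these are 0.1427/0.1625 = 0.878 and 0.1135/0.1625 = 0.698. Cases per person-year are then 0.1625 in both groups, so the rate ratio is 1.

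**Sensitivity.** At 445 v 89, losses of 10% v 30% give about 5.6%. In a second set-up, all patients are followed 12 months, controls a shorter common time, and the 12-month risk is 5% to 20%. At 445 v 89 the false rejection rate is then 4.7% to 6.2% with controls followed 10.8 months, 5.8% to 15.3% at 9 months and 12.1% to 56.5% at 6 months. With an assumed 1355 v 271 (5:1 on the planned controls), 9 months gives 11.6% to 41.1%.

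**The case against.** - **Denominator.** A reader might infer that people who fall silent are counted as event-free for the year. The protocol does not say so; it has no denominator or missing-data rule, and one may sit in the SAP. This stands as a limit on the wording. It does not rescue the test, since both usual denominators are biased when losses differ. Excluding everyone lost, including those who had already become cases, would return 15% in both groups under the assumptions above. It would discard observed cases, and the protocol does not specify it.
- **Serious events.** A reader might infer that all hospitalizations and deaths share the 12-month problem. The text does not support that. The window belongs to COVID-19 surveillance, and serious events are described beside the fixed-window diary.
- **Is the comparison planned?** OUTCOMES does not list COVID-19 cases, effectiveness is undefined, and the swab sentence refers to patients. This lowers the priority. The analysis section still names effectiveness and fixes the test for it.
- **Differential loss.** It is assumed. Controls are vaccinated at the same hospital and are compared with patients again 6 months after dose 2, so similar retention is possible, and equal losses give no bias here. The effect is small for moderate gaps.
- **Pairing of 445 and 271.** It is illustrative. The protocol pairs 445 with 89, and the 271 controls come from separate disease-specific needs.
- **Contact dates.** The protocol mentions weekly messages but not that replies are logged. If people reply mainly when ill, censoring at the last reply would be informative.

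**Conclusion.** The point holds for COVID-19 cases found by surveillance, and for hospital admissions for COVID-compatible illness found the same way. For these, a proportion test does not fit follow-up that may vary between people and between groups.

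The size rests on assumed losses and an assumed infection rate. It ranges from no bias when losses are equal, through about 8% false rejection at 10% v 30% lost, to about 19% at 10% v 50% lost. A true hazard ratio of 1.5 can be diluted from a risk ratio of 1.44 to 1.30. The documents do not show that follow-up will differ; they show only that the stated analysis has no protection if it does. The point does not extend to serious adverse events in general or to the diary reactions. Because COVID-19 cases are not a listed primary outcome, this is a worthwhile correction of modest priority.

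**What to change.** In STATISTICAL ANALYSIS, limit the chi-square or Fisher rule to the fixed-window diary reactions and the adverse events assessed in those windows. For COVID-19 cases, and for hospitalizations for COVID-compatible illness found by the same surveillance, state one of:

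- incidence per person-time in each group, with a patient/control rate ratio and 95% CI; or
- Kaplan-Meier estimates with a log-rank or Cox comparison.

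Censor at the last documented contact or visit, and report the follow-up time in each group.

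The cost is a little more programming and a last-contact date kept for every participant, which the protocol does not currently say is recorded. No extra visits or samples are needed. The method assumes that censoring is unrelated to infection. Defining contact in a way that does not depend on the participant being ill, and comparing response by group, would help to judge that.
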